# An open-label randomised controlled trial evaluating the efficacy of a meningococcal serogroup B (4CMenB) vaccine on *Neisseria gonorrhoeae* infection in gay and bisexual men: the MenGO study protocol

**DOI:** 10.1186/s12889-023-15516-y

**Published:** 2023-03-30

**Keywords:** Gonorrhoea, *Neisseria gonorrhoeae*, Sexually transmitted infection (STI), Gay and bisexual men (GBM), Men who have sex with men (MSM), 4CMenB, Bexsero, Vaccine

## Abstract

**Background:**

Gonorrhoea is an ongoing public health concern due to its rising incidence and the emergence of antibiotic resistance. There are an estimated 82 million new *Neisseria gonorrhoeae* infections each year, with several populations at higher risk for gonococcal infection, including gay and bisexual men (GBM). If left untreated, infection can lead to serious morbidity including infertility, sepsis and increased risk of HIV acquisition. Development of a gonorrhoea vaccine has been challenging, however there is observational evidence that serogroup B meningococcal vaccines, used to protect against the closely related bacteria *Neisseria meningitidis*, could provide cross-protection against *N. gonorrhoeae.*

**Methods:**

The MenGO (Meningococcal vaccine efficacy against Gonorrhoea) study is a phase III open-label randomised control trial in GBM to evaluate the efficacy of the four-component meningococcal serogroup B vaccine, 4CMenB, against gonorrhoea. A total of 130 GBM will be recruited at the Gold Coast Sexual Health Clinic, Australia, and randomised to either receive 2 doses of 4CMenB or no intervention. Participants will be followed up for 24 months with testing for *N. gonorrhoeae* and other sexually transmissible infections every three months. Demographics, sexual behaviour risk, antibiotic use, and blood samples for analysis of *N. gonorrhoeae-*specific immune responses, will be collected during the study. The primary outcome is the number of *N*. *gonorrhoeae* infections in participants over 2 years measured by nucleic acid amplification test (NAAT). Secondary outcomes are vaccine-induced *N. gonorrhoeae-*specific immune responses, and adverse events in trial participants.

**Discussion:**

This trial will determine if the 4CMenB vaccine is able to reduce *N. gonorrhoeae* infection. If shown to be effective, 4CMenB could be used in gonococcal prevention. Analysis of 4CMenB-induced immune responses will increase understanding of the type of immune response needed to prevent *N. gonorrhoeae*, which may enable identification of a potential correlate of protection to aid future gonorrhoea vaccine development.

**Trial registration:**

The trial has been registered on the Australian and New Zealand Clinical Trials Registry (ACTRN12619001478101) on 25 October 2019.

**Supplementary Information:**

The online version contains supplementary material available at 10.1186/s12889-023-15516-y.

## Background

*Neisseria gonorrhoeae* is a significant healthcare challenge worldwide, causing an estimated 82 million cases/year of the sexually transmitted infection (STI) gonorrhoea [1]. Gonorrhoea cases have risen in many regions in recent years (e.g., 45% increase in the USA in the 5 years between 2016 and 2020 [2] and 144% increase in Australia in the 10 years between 2011 and 2020 [3]). Gonorrhoea infection is more prevalent in particular risk groups, including gay and bisexual men (GBM) [4]. GBM who are taking HIV pre-exposure prophylaxis (PrEP) have an incidence rate of 37.8 cases per 100-person years [5]. Gonorrhoea is increasingly difficult to treat due to ongoing emergence of antimicrobial resistance [6]. *N. gonorrhoeae* has developed resistance to all classes of antibiotics used to treat it since the 1940s, with new treatment regimens needed every 5–10 years [7]. In particular, treatment for pharyngeal gonorrhoea remains a challenge, with lower treatment efficacy for current and new antibiotic regimens [8], contributing to the emergence of antibiotic resistance and onward transmission. Since 2013, the WHO and CDC have highlighted gonorrhoea as an “urgent” public health threat [9–11] and in 2018, ‘super gonorrhoea’, resistant to all routine antibiotics was reported in the UK [12] and Australia [13].

*N. gonorrhoeae* infection can result in a range of clinical outcomes, which vary by site of infection and by sex [14]. Pharyngeal and anal infections are typically (~ 90%) asymptomatic, while genital tract infection is more frequently symptomatic. In men, genital infection is typically characterised by symptomatic urethritis, but may be asymptomatic in up to 10% of patients [15]. Complications of untreated infection in men include urogenital tract abscesses, orchitis, and prostatitis [16]. In women, 50–80% of lower genital tract gonorrhoea infections remain asymptomatic, and hence are frequently untreated. Ascending infection to the Fallopian tubes occurs in up to 45% of infected women, and can result in serious complications including pelvic inflammatory disease, ectopic pregnancy, spontaneous abortion, pre-term or low weight birth, stillbirth, neonatal blindness and infertility [16]. Gonorrhoea increases the risk of HIV transmission, and is a major contributor to the ongoing HIV epidemic [14]. Hence, the development of a vaccine to prevent gonorrhoea is urgently needed [9] .

Despite more than a century of research, there is currently no gonorrhoea vaccine. This is largely due to the fact that gonococcal infection does not protect against subsequent infection, therefore there are no correlates of protection from natural immunity to guide vaccine development [14]. Moreover, humans are the only natural host for *N. gonorrhoeae* and there is no animal model that accurately mimics human infection and transmission. Thus, there are limited tools to enable discovery and evaluation of potentially protective vaccine candidates [14]. However, it has been reported that meningococcal serogroup B vaccines, used to protect against the closely related bacteria *Neisseria meningitidis*, may be associated with reduced incidence of *N. gonorrhoeae* infection [17–20].

The meningococcal B outer membrane vesicle (OMV) vaccine MeNZB™ was used to vaccinate > 1 million people in New Zealand between 2004–2008 in response to a meningococcal B epidemic [21]. A retrospective case-control study of this cohort showed that MeNZB™-vaccinated individuals were significantly less likely to contract gonorrhoea compared to unvaccinated controls, with a predicted vaccine efficacy of 31% [17]. Although modest, this was the first time a vaccine has been associated with any protection against gonorrhoea [18]. A broader spectrum four-component meningococcal B vaccine, 4CMenB (marketed as Bexsero®) is now available and contains the MeNZB™ OMVs plus three recombinant protein antigens (NadA, and the fHbp-GNA2091 and NHBA-GNA1030 fusions) [22]. Recent observational cohort studies using data linkage have demonstrated 4CMenB vaccine efficacy of 32–40% in preventing gonorrhoea infection in young adults [19, 20]. Mathematical modelling of hypothetical gonococcal vaccines has indicated that even a vaccine with a modest effectiveness of ~ 30% could reduce the population prevalence of gonorrhoea by ~ 50% within 20 years in a general heterosexual population [23] and by > 40% within 2 years in a GBM population [24].

The level of antigenic identity between *N. meningitidis* and *N. gonorrhoeae* has been suggested to be responsible for the possible cross protection between the meningococcal serogroup B vaccines and *N. gonorrhoeae.* Bioinformatic analysis has identified that a homologue of 20 of the 22 major meningococcal OMV proteins on the 4CMenB vaccine are present in *N. gonorrhoeae* (16 proteins have > 90% identity, 2 proteins have > 80% identity to the meningococcal vaccine antigen), and the 4CMenB NHBA antigen shares > 67% identity to NHBA from *N. gonorrhoeae* strains [25]. Furthermore, human anti-4CMenB antibodies are cross-reactive with *N. gonorrhoeae* [25]. The 4CMenB vaccine has been licensed in more than 40 countries worldwide, and the safety and side effects of the vaccine have been well documented [26]. 4CMenB is licensed in Australia for active immunisation against invasive disease caused by *N. meningitidis* group B strains in people > 2 years of age (two doses with an interval of ≥ 1 month between doses) [27].

## Methods

### Aims and hypotheses

The MenGo trial aims to determine if vaccination with the meningococcal vaccine 4CMenB can reduce the incidence of *N. gonorrhoeae* infection in GBM over 2 years, and to investigate vaccine induced immune responses during the study period. We hypothesise that 4CMenB could reduce the risk of acquiring gonorrhoea and that investigation of 4CMenB-induced antibodies that are cross-reactive with *N. gonorrhoeae* could reveal the mechanism of 4CMenB-induced protection against *N. gonorrhoeae* infection.

### Study design and setting

MenGO is a Phase III open-label unblinded randomised control trial of 4CMenB vaccination of GBM to protect against *N. gonorrhoeae* infection. The study design is shown in Fig. 1. Participants will be randomly assigned by 1:1 allocation to either: (1) the ‘4CMenB vaccine arm’ who will be vaccinated at baseline and 3 months with 4CMenB; or (2) the unvaccinated ‘no treatment arm’. An STI screen as per the Australian STI guidelines [28] will occur at baseline and at 3 monthly study visits over 2 years. Blood will be collected for antibody analysis at 0, 3, 6, 12, and 24-month visits, and information regarding demographics, concurrent medication, previous gonorrhoea infections, antibiotic use and sexual behaviour risks will be collected at each visit. The trial will be conducted in accordance with the guidelines for Good Clinical Practice (GCP) and will satisfy Consolidated Standards of Reporting Trials (CONSORT) reporting conventions [29].

**Fig. 1 Fig1:**
[figure not shown]
Overview of MenGO Trial design

### Eligibility criteria for participants

The study is limited to GBM attending a public sexual health clinic, who are at a high and ongoing risk of acquiring *N. gonorrhoeae*.

#### Inclusion criteria

GBM who are:

i.Between 18 and 50 years of age.ii.Able to understand spoken and written English.iii.Men who have sex with other men.iv.Able to participate in study procedures including attending for all study visits.v.At risk of acquisition of gonorrhoea at the time of enrolment into the study.vi.Agree to be contacted via phone/ email by the study team.

AND are:

Currently taking HIV pre-exposure prophylaxis (PrEP) at the time of enrolment ORHave been diagnosed with gonorrhoea in the last 3 months.

#### Exclusion criteria

Participants will be excluded from participation if they have:

i.Documented allergy to latex and/ or kanamycin.ii.Confirmed previous history of vaccination for meningococcal B with 4CMenB.iii.Contraindications to receiving the meningococcal B vaccine which include:

Anaphylaxis following a previous dose of any meningococcal vaccine.Anaphylaxis following any vaccine component.

iv.Participants who are currently recommended and funded to receive 4CMenB [30] including participants who have:

Sickle cell disease or other haemoglobinopathies.Congenital or acquired asplenia (e.g., plenectomy or hyposplenia).Defects in, or deficiency of, complement components including factor H, factor D or properdin deficiency.Current or planned future treatment with eculizumab (a monoclonal antibody directed against complement component C5).

Previous meningococcal disease and previous vaccination with the strain specific meningococcal B vaccine MeNZB™ is not a contraindication for receiving 4CMenB.

### Intervention

Participants will be randomly assigned to either the ‘4CMenB vaccine arm’ or the ‘no treatment arm’ of the study. Participants allocated to the vaccine group will receive a 2-dose schedule of 4CMenB (first dose at baseline visit, second dose at 3-month visit). For each dose, 0.5mL of 4CMenB will be administered by deep intramuscular injection, preferably in the deltoid muscle region of the upper arm. Participants allocated to the no treatment control group will not receive any treatment.

### Outcomes

Table 1 lists primary and secondary outcomes alongside key study objectives and endpoints.

#### Primary outcome

(i)Number of *N*. *gonorrhoeae* infections in participants at any anatomical site over 2 years, diagnosed by nucleic acid amplification test (NAAT).

#### Secondary outcomes

(ii)Level and function of *N. gonorrhoeae-*specific antibodies.(iii)Number of serious adverse events (SAEs) reported where the cause has been determined to be related to the study treatment.(iv)Number of participants consented to the trial compared to number of participants where pre-screening was performed.

**Table 1 Tab1:** Study objectives, outcomes and endpoints

Objectives	Outcome / Endpoint
**Primary**	
Determine if vaccination with 4CMenB reduces the incidence of gonorrhoea	Number of *N*. *gonorrhoeae* infections at any anatomical site over 2 years, diagnosed by nucleic acid amplification test (NAAT).
**Secondary**	
Characterise humoral immune response in 4CMenB-vaccinated serum	Level and function of *N. gonorrhoeae-*specific antibodies.
Determine the safety and tolerability of 4CMenB in GBM aged 18–50 years	Number of SAEs reported where the cause has been determined to be related to the study treatment
Determine the uptake and feasibility of 4CMenB as a preventative strategy for gonorrhoea in GBM attending sexual health services	Number of participants consented to the trial compared to number of participants where pre-screening was performed

### Sample size

A target of 130 participants will be recruited into the study. To detect a reduction in gonococcal prevalence from 30% (based on a gonococcal prevalence of 29.4% in patients taking PrEP at Gold Coast Sexual Health Service) to 10% (assuming a vaccine efficacy of 30%, based on the predictive MeNZB™ [17]) with 80% power at a significance level of 0.05 using the proportions test, 112 participants will need to be recruited into equal groups of 56 (G*Power 3.1). To account for an attrition or loss to follow up at a rate anticipated to be less than 10% the total recruiting target is 130. The Gold Coast Sexual Health Service see more than 10,000 patients per annum of which approximately 1,700 are GBM, which should enable adequate recruitment to reach the target sample size.

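### The sample size labels a fall from 30% to 10% as 30% vaccine efficacy; it is 67%, and at 30% efficacy the power is roughly 15–35%, not 80%

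*Protocol article*

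**What the plan says.** The Sample size section of the protocol article sets the target as follows: "To detect a reduction in gonococcal prevalence from 30% (based on a gonococcal prevalence of 29.4% in patients taking PrEP" at the site, "to 10% (assuming a vaccine efficacy of 30%, based on the predictive MeNZB" study, "with 80% power at a significance level of 0.05 using the proportions test". This gives 112 participants, 56 per arm, by G\*Power 3.1. The number is raised to 130 (65 per arm in the Randomisation section) for an expected loss below 10%.

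The Background gives the source of the efficacy figure. Recipients of the earlier vaccine were "significantly less likely to contract gonorrhoea compared to unvaccinated controls, with a predicted vaccine efficacy of 31" per cent. For the trial vaccine itself it reports "4CMenB vaccine efficacy of 32–40% in preventing gonorrhoea infection in young adults". Both are relative reductions.

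The primary outcome is the number of infections at any site over two years. The Statistical methods section plans Fisher's exact test, Poisson regression with a rate ratio and 95% CI, and a GEE version if participants have repeat infections. The abstract says: "This trial will determine if the 4CMenB vaccine is able to reduce" infection.

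**The concern.** The justification and the effect stand in one sentence and cannot both be true. A fall from 30% to 10% is a 67% relative reduction or a 20-point absolute one, so neither reading gives 30%.

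The paragraph therefore presents the trial as having 80% power for the efficacy its evidence supports, when the calculation was done for an effect about twice as large. The Background treats an efficacy near 30% as worth having at population level, so this is the effect the trial should be able to speak to. If true efficacy is about 30%, a non-significant result is the likeliest outcome. Anyone relying on the sample-size paragraph (ethics committee, monitoring committee, later meta-analysts) could read that result as evidence against an effect the trial was too small to detect.

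**Working it through.** **Inputs.** Sample size section: control risk 30%, vaccine risk 10%, stated efficacy 30%, 80% power, α = 0.05, sidedness not stated, 56 per arm rising to 65. Background: 37.8 infections per 100 person-years in men on PrEP. Study design: two years of follow-up. Assumption from outside the documents: a frailty variance of k = 1 as an example of overdispersion; k = 0 is pure Poisson.

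**1. Reproducing 112.** With a one-sided Fisher's exact test for 30% versus 10% (full enumeration of both binomials), power is 79.4% at 55 per arm and 80.2% at 56. So 56 is the first size to reach 80%, and 112 is reproduced. Two-sided methods do not give it: the pooled z test needs 62 per arm and Fisher about 69. The arithmetic is sound for 30% versus 10%; the error is in the effect fed into it.

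**2. The efficacy implied.** 1 − 0.10/0.30 = 0.667. Conversely, 0.30 × (1 − 0.30) = 0.21.

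**3. Power for 30% versus 21%.** For the two-sided pooled z test, with p̄ = 0.255:

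- √(2 × 0.255 × 0.745) = 0.616 and √(0.30 × 0.70 + 0.21 × 0.79) = 0.613.
- Power = Φ[(0.09√n − 1.960 × 0.616)/0.613], which is Φ(−0.87) = 19% at n = 56 and Φ(−0.79) = 22% at n = 65.
- Size for 80% power = (1.960 × 0.616 + 0.842 × 0.613)²/0.09² = 367 per arm.

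| Test, 30% v 21% | 56 per arm | 65 per arm |
|---|---|---|
| z, two-sided | 19% | 22% |
| Fisher, two-sided | 14% | 16% |
| z, one-sided | 29% | 32% |
| Fisher, one-sided | 22% | 26% |

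**4. Power on the count of infections.** Assuming complete follow-up, expected events are E0 = 65 × 0.378 × 2 = 49.1 in controls and E1 = 0.70 × 49.1 = 34.4 in the vaccine arm. The variance of the log rate ratio is 1/E0 + 1/E1 + 2k/n, and |ln 0.70| = 0.357.

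- k = 0: SE = 0.222; power = Φ(0.357/0.222 − 1.960) = 36%.
- k = 1: SE = 0.283; power = Φ(0.357/0.283 − 1.960) = 24%.
- With 58 per arm (65 less 10%): 33% and 22%.
- Size for 80% power: (1.960 + 0.842)² × (1/0.756 + 1/0.529 + 2k)/0.357², about 198 per arm for k = 0 and 322 for k = 1.

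**5. The top of the cited range, 40% efficacy.** Two-sided power for 30% versus 18% is 25% (Fisher, 56 per arm) to 36% (z, 65 per arm). On counts with 65 per arm it is 59% (k = 0) or 42% (k = 1); with 58 per arm, 54% or 38%.

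**6. Smallest efficacy detectable with 80% power, two-sided.** On proportions (pooled z): 69% at 56 per arm, 65% at 65. On counts: 50% (k = 0) to 59% (k = 1) at 65 per arm, and 53% to 62% at 58.

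**The case against.** No other section corrects the sentence, and the contradiction is not an effect of condensing a longer protocol, because the article states it outright. The fair objections concern its size.

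- **The primary outcome is a count, so 367 per arm is the less favourable figure.** This stands. On counts the requirement is about 198 to 322 per arm, still three to five times 65.
- **A null result is not the likeliest outcome across all of 30–40%.** This stands in part. At 40% efficacy with pure Poisson counts, power is 59%, so the statement that a null result is likely should be kept to efficacies near 30%.
- **The 15–35% range depends on assumptions.** True. The calculated values run from 14% to 36%. The trial also enrols men with recent gonorrhoea, whose incidence may exceed 37.8. If it were 50–60 per 100 person-years (an assumption; the documents give no figure), power at 30% efficacy with 65 per arm would be 45–52% for Poisson counts, or 28–30% with k = 1. Only the most favourable combination comes near 80%: at 60 per 100 person-years, 40% efficacy, no overdispersion and no losses, E0 = 78, E1 = 46.8, SE = 0.185 and power is 79%.
- **The planned calculation appears one-sided.** It does, and one-sided power at 30% efficacy is 22–32%. The Statistical methods section, however, uses a two-sided 95% CI.
- **Estimation is already planned.** The rate ratio and rate difference come with confidence intervals, and how a null result will be read may be left to an analysis plan that is not shown. That part of the remedy is therefore optional.

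**Conclusion.** The concern holds, and the paragraph is wrong as written. The 67% figure is exact and needs no assumption. The 112 participants derive from that effect and not from the 30% efficacy named beside it.

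At 30% efficacy, power is about 15–35% across tests, sidedness, arm sizes of 56 to 65 and the count analysis at the protocol's own incidence. At that incidence it stays well below 80% throughout 30–40%. The proportion figures rest on the stated 30% control risk, which is given as a prevalence without a time frame. The count figures rest on 37.8 per 100 person-years, two full years of follow-up unless 58 per arm is stated, and an illustrative frailty variance of 0 to 1.

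**What to change.** In the Sample size section:

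- State that 30% to 10% corresponds to an assumed efficacy of 67%, and remove the claim that it represents 30% efficacy drawn from the earlier vaccine study.
- Name the test and its sidedness.
- Keep 130 participants, and report power at 30% and 40% efficacy for the count outcome, with the incidence, follow-up and overdispersion assumed.
- Give the smallest efficacy detectable with 80% power, about 50–60% on counts.

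It would also help, though it is optional here, to say before results are known that a non-significant finding will be interpreted from the confidence interval for efficacy and will not be taken to exclude 30–40%.

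The cost is a rewritten paragraph and a less favourable power statement. No extra participants and no design change are needed.

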### Randomisation and allocation

Participants will be randomized 1:1 to 2 groups of 65 – the ‘4CMenB vaccine arm’ or the ‘No vaccine arm’. A biostatistician independent of the clinical researchers will use the ralloc package of Stata 17 (College Station, Tx., USA) to perform block randomization with blocks of size 2–6. Allocations will be placed in sequentially numbered sealed envelopes and kept in a locked cupboard with restricted access to the area (security pass protected). Randomised allocation will only be performed once written informed consent has been obtained. Investigators will allocate study participants from the sequential sealed envelopes, ensuring that there is blinding of the randomisation process.

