### Statistical methods

Data analysis will be performed by statisticians at the Gold Coast Hospital and Health Service (GCHHS) who are not involved in other study procedures, to reduce chance of bias in the statistical analysis. The number and percentage of participants with NAAT confirmed *N. gonorrhoeae* from any anatomical site will be presented along with 95% confidence interval (CI) at the completion of the study by treatment group. Total observation time will also be recorded. Associations between 4CMenB vaccination status and the incidence of *N. gonorrhoeae* infection will be investigated using Fisher’s exact test and univariate Poisson regression. The incident rate ratio (IRR) with 95% CIs of incidence of *N. gonorrhoeae* infection in the vaccinated group compared to the unvaccinated group will be calculated. Demographic and clinical characteristics of the 4CMenB vaccinated group and the “no vaccine” group will be compared. If any variables are seen to be different between groups (not expected due to randomization) these will be included in a multivariable Poisson regression model along with 4CMenB vaccine predicting *N. gonorrhoeae* infection. The difference in incidence rates of *N. gonorrhoeae* infections between the study treatment and no treatment at the end of the 2-year study period will also be calculated along with 95% CI. The study treatment will be considered effective if the lower limit of the 2-sided 95% CI for the difference between the incidence rates of gonorrhoea in the study treatment group is 30% lower than the no treatment group. Further analyses may be performed based on the observed differences between the treatments in some subgroups. If it is the case that individual participants record more than one incidence of *N. gonorrhoeae* infection in the period of the study, the same analyses will be performed but using a generalized estimating equations (GEE) approach to Poisson regression to account for within participant correlation.

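### The 112 participants given for 80% power match a one-sided Fisher's exact test; under the two-sided standard used to judge efficacy, 56 per arm gives about 69% to 79%

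*Protocol article*

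**What the plan says.** The Sample size section of the protocol article gives the whole calculation:

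- Control arm: "To detect a reduction in gonococcal prevalence from 30% (based on a gonococcal prevalence of 29.4% in patients taking PrEP".
- Vaccine arm: "to 10% (assuming a vaccine efficacy of 30%, based on the predictive MeNZB™ [17".
- Error rates and test: "with 80% power at a significance level of 0.05 using the proportions test", with G*Power 3.1 cited as the software. Neither the sidedness nor the exact form of the test is given.
- Result: "112 participants will need to be recruited into equal groups of 56".
- Allowance for loss: "attrition or loss to follow up at a rate anticipated to be less than 10% the total recruiting target is 130".

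Randomisation and allocation confirms the enrolled size: "Participants will be randomized 1:1 to 2 groups of 65".

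Statistical methods names the comparison as Fisher's "exact test and univariate Poisson regression". It bases the declaration of efficacy on the "lower limit of the 2-sided 95% CI for the difference" in incidence rates. No section states or justifies a one-sided test.

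**The concern.** A sample size at a one-sided 5% level is smaller than one at a two-sided 5% level for the same effect and power. If 112 was derived one-sided while the results are judged two-sided, the stated 80% is not the power of the planned comparison.

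The figure matters because the trial is small and ends in a yes-or-no statement of efficacy. Anyone interpreting a null result will take the risk of missing a true 30%-to-10% effect to be 20%. If that risk is nearer 30% for the exact test the plan names, a null result would be read as stronger evidence against the vaccine than it is.

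**Working it through.** **Inputs.** p1 = 0.30, p2 = 0.10, level 0.05, power 0.80, 56 per arm (Sample size); 65 per arm enrolled (Randomisation and allocation). Loss is stated as below 10%. I take the full 10% as the planning case: 130 × 0.90 = 117, about 58 per arm.

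**Step 1: reproduce 112.** Let X ~ Bin(n, 0.30) and Y ~ Bin(n, 0.10) be independent. Power is the sum of P(X = x)·P(Y = y) over all tables with p ≤ 0.05. For one-sided Fisher:

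- n = 55: 79.4%, the highest of all n from 40 to 55
- n = 56: 80.2%

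The smallest n is therefore 56 per arm, 112 in total, an exact match. An enumerated continuity-corrected chi-square gives the same power at 55 and 56, and it is also one-sided.

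**Step 2: try the two-sided forms.** For the pooled z-test, with p̄ = 0.20:

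n = [z₀.₉₇₅·√(2p̄(1−p̄)) + z₀.₈₀·√(p1(1−p1) + p2(1−p2))]² / (p1−p2)²

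= [1.960·√0.32 + 0.842·√0.30]² / 0.04 = 61.6, so 62 per arm (124).

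| Two-sided method | Total N for 80% |
|---|---|
| Unpooled z, enumerated | 116 |
| Unpooled z, formula | 118 |
| Pooled z, enumerated | 118 |
| Arcsine | 120 |
| Pooled z, formula | 124 |
| Fisher's exact, enumerated | 138 |
| Pooled z with continuity correction | 144 |

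None gives 112. For Fisher, 68 per arm gives 79.97% and 69 per arm gives 80.7%. One-sided z formulas do not give 112 either: pooled z gives 98, and 116 with continuity correction.

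**Step 3: two-sided power at the sizes that matter.** The pooled z formula is Φ{[0.20·√n − 1.960·√0.32] / √0.30}. The other columns are enumerated.

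| Per arm | Fisher | Pooled z, formula | Pooled z, enumerated | Unpooled z, enumerated |
|---|---|---|---|---|
| 56 (the stated 112) | 69.4% | 76.1% | 78.1% | 78.8% |
| 58 (130 less 10%) | 71.6% | 77.5% | 79.7% | 80.4% |
| 65 (130, no loss) | 77.5% | 82.1% | 83.2% | 84.7% |

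**Step 4: enrolment needed to keep 80% two-sided after 10% loss.** N/(1 − 0.10) is 118/0.9 → 132 (enumerated pooled z), 124/0.9 → 138 (pooled z formula) and 138/0.9 → 154 (Fisher). The target is 130.

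**The case against.** The arithmetic is not in dispute; the objections concern what it can be held against.

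1. **Sidedness is inferred.** The protocol never says the calculation was one-sided. That is true, and the exact match is only strong circumstantial evidence. But the error does not depend on how 112 was reached, because no two-sided test tried gives 80% at that size.

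2. **Fisher's test is not the decision rule.** It is listed beside Poisson regression, its own sidedness is not stated, and efficacy is declared from an interval for the difference in incidence rates with a 30% criterion. None of the figures above is the power of that rule. This stands as a limit on what can be claimed. It does not rescue the 80%, which the protocol itself ties to a test of proportions.

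3. **At the enrolled size, a z-type test is close to target.** Enumerated z-tests give 79.7% (pooled) or 80.4% (unpooled) at 58 per arm, and more with less loss. This also stands. The practical shortfall at 130 recruited belongs mainly to Fisher's test.

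4. **A larger problem sits in the same sentence.** A 30% efficacy applied to 30% gives 21%, not 10%, and two-sided power at 56 per arm would then be about 19%. That is a separate error. The sidedness mismatch remains even if 30% versus 10% is accepted.

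**Conclusion.** The concern holds. The claim that 112 evaluable participants give 80% power is wrong for a two-sided 5% comparison of 30% with 10%. The overstatement is about 11 points for Fisher's test (69.4%) and 1 to 4 points for z-type tests (76.1% to 78.8%).

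For 130 recruited with 10% loss, Fisher's test falls about 8 points short (71.6%), while z-type tests run from 77.5% to 80.4%. With no loss at all, Fisher's test still stops at 77.5%; z-type tests pass 80%.

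These figures assume the protocol's own 30% and 10%, equal arms, one binary outcome per participant and a conventional two-sided 0.05 level. They say nothing about the power of the Poisson analysis or of the interval-based efficacy criterion.

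**What to change.** Replace the power statement with one that names the test and its sidedness, for example: at a two-sided 0.05 level, with 130 randomised and up to 10% lost (about 58 per arm), power to detect 30% versus 10% is about 72% by Fisher's exact test and about 78% by the pooled z-test formula (close to 80% if that test is enumerated). Drop the claim that 112 gives 80%. Better still, report power for the count-based model that estimates the rate ratio, with its assumptions stated. Settle the effect size in that sentence at the same time, since any restated figure depends on it.

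Keep the two-sided 5% level in the analysis; moving to a one-sided test to preserve the 80% would weaken the efficacy standard.

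The cost is one corrected statement and a less favourable power figure. No extra participants and no change to trial conduct are needed.
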